### Data collection and sampling

Data collection will include routine trial logs to document the number of TB patients screened, further assessed, and those receiving CBT intervention. Screening penetration will be measured by calculating the proportion of TB patients screened using PHQ-2 and their referral rates to mental health services. Usability and sustainability will be assessed by recording the time required to complete PHQ-2 screening, dropout rates, and follow-up adherence among CBT recipients.

The expenses related to the implementation will be evaluated by examining the costs and cost-effectiveness measures used during the trial. This evaluation will consider the expenses of the CONTROL intervention and enhanced treatment as usual (ETAU). An adapted version of the Client Service Receipt Inventory (CSRI) will be utilized to assess costs, similar to our previous methodology for cost-effectiveness analysis of psychological intervention in the region [35]. This assessment will encompass visits to primary care and outpatient services, medication costs, travel time, transportation expenses, and days lost from work. Current prices or unit costs will be obtained from national sources, validated, and, if necessary, extrapolated from UK equivalents to be applied to these resource categories, allowing for an estimate of overall and individual costs.

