**3**	**Adoption**	Adoption refers to the early uptake, utilization, and initial implementation of the CBT intervention within The CONTROL Trial and their intention to integrate it into routine TB care	The Applied Mental Health Research Group (AMHR)-adoption subscale	8-week	10% of randomly selected patients in the intervention arm
**4**	**Acceptability**	Acceptability refers to participants' satisfaction and perceptions regarding various aspects of the CBT intervention delivered under The CONTROL Trial, including its content, complexity, ease of participation, delivery method, and perceived credibility	The Applied Mental Health Research Group (AMHR)-acceptability subscale	8-week	10% of randomly selected patients in the intervention arm
			Acceptability of Intervention Measure (AIM)	8-week	10% of randomly selected patients in the intervention arm
			Retention in the number of sessions attended and % of those who dropped out of the intervention	After the definitive trial, all relevant data will be retrieved from the trial team's data logs	
**5**	**Fidelity**	The extent to which the CBT intervention is delivered as intended, ensuring adherence to the structured protocol, maintaining integrity in session delivery, and upholding the quality of program implementation by TBHWs within routine TB care	The Revised Cognitive Therapy Scale (CTS-R)	Ongoing process (first to sixth week post-randomization)	10% of all the sessions, delivered by the DOTS facilitator
			CBT content delivery assessment scale		
**6**	**Penetration**	The extent to which the CBT intervention is institutionalized within the TB care system, assessing its spread across healthcare facilities and the level of service access for TB patients needing psychological support	Data from the routine trial logs	After the definitive trial, all relevant data will be retrieved from the trial team’s data logs	
**7**	**Sustainability**	The extent to which the CBT intervention is maintained, continued, and durably integrated into routine TB care beyond the CONTROL trial, assessing its incorporation into health system structures, institutionalization within policies, and sustained use by TBHWs and patients	Administrative Data logs	After the definitive trial, all relevant data will be retrieved from the trial team’s data logs	

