## Penetration, sustainability and implementation costs

### Data collection tool

Penetration and sustainability will be assessed using routine trial logs after the definitive trial, focusing on policymakers’ acceptance of mental health measures and evaluating the sensitivity and specificity of the Patient Health Questionnaire short version (PHQ-2) in routine depression screening within the TB care program. In the CONTROL definitive trial, TBHWs will (pre)screen all patients presenting at the selected TB centers on PHQ-2 and assess the frequency of depressed mood and anhedonia over a 2-week period. Being a simple two-question screening tool, it will be easy to implement in the routine, and could be used by healthcare workers at TB centers [15]. The data will also help explore the potential adaptation of PHQ-2 to screen depression in other chronic infections prevalent in the region, providing robust insights into the implementation and scalability of the study measures across diverse healthcare settings.

Implementation costs are influenced by three main factors: the treatment’s complexity, the implementation strategy’s intricacy, and the setting where the treatment is delivered. Consequently, the total cost of implementation depends on the specific intervention, the chosen strategy, and the delivery environment [23]. Implementation costs will be measured using the Client Service Receipt Inventory (CSRI) [34]. The evaluation will mainly be approached from the standpoint of the health system, including (a) expenses associated with the implementation of the intervention during the trial, (b) utilization of additional healthcare and related services by the participants, and (c) costs incurred by patients and their families.

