## Data analysis

### Quantitative data analysis

We will employ descriptive and inferential statistical methods to analyse the CONTROL study and CBT intervention’s implementation outcomes—acceptability, appropriateness, adoption, and feasibility. Data from the AIM, IAM, FIM, and AMHR scales will be analysed to assess central tendencies and variability. Regression analyses will be conducted to explore relationships between implementation outcomes and participant characteristics. Retention and enrolment rates will be calculated as proportions, with chi-square tests to examine group differences.

Two independent reviewers, both experts in CBT, will assess a randomized selection of 10% of the audio-recorded CBT sessions to analyse the fidelity of the CONTROL CBT intervention through CTS-R and a CBT delivery assessment checklist. According to the Newcastle Cognitive Therapy Centre, a minimum competence standard is set at 36, with higher scores indicating greater therapeutic competence. Descriptive statistics will summarize the distribution of scores across sessions, and inter-rater reliability will be assessed using intraclass correlation coefficients to ensure consistency between reviewers. Similarly, the delivery assessment checklist evaluates adherence to the intervention’s content, and for each session, item scores will be aggregated to produce a total adherence score. Descriptive statistics will describe the adherence levels, and inter-rater reliability will be calculated to confirm reviewer consistency.

Penetration analysis will calculate the proportion of TB patients screened with the PHQ-2 and those referred for mental health services. High screening and referral rates will indicate successful penetration of mental health assessments into the TB program. Cost analysis will utilize data from the CSRI to compute the total and per-patient costs of implementing the mental health interventions. This will include direct costs (e.g., training, therapy sessions) and indirect costs (e.g., patient travel, lost productivity). The cost-effectiveness of the intervention will be evaluated by comparing the incremental costs to the health outcomes achieved, such as reductions in depression and anxiety symptoms.

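### The sustainability indicators observe no use after the trial, and the penetration rule does not tie referral to patients in need

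*Protocol article*

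**What the plan says.** **Sustainability.** Table 2 defines it as "The extent to which the CBT intervention is maintained, continued, and durably integrated into routine TB care beyond the CONTROL trial", and adds anchoring in policy and lasting use by health workers and patients. The tool in that row is administrative data logs, retrieved after the definitive trial. Under Penetration, sustainability and implementation costs, the Data collection tool text says: "Penetration and sustainability will be assessed using routine trial logs after the definitive trial". It adds that this assessment will focus on policymakers' acceptance and on the sensitivity and specificity of the PHQ-2. The Data collection and sampling text then names the indicators: "Usability and sustainability will be assessed by recording the time required to complete PHQ-2 screening, dropout rates, and follow-up adherence among CBT recipients". The Quantitative data section lists what the logs contain: prescreening, screening, recruitment, retention and CBT records.

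**Penetration.** Table 2 describes it as institutionalisation of CBT, "assessing its spread across healthcare facilities and the level of service access for TB patients needing psychological support". The measurement is: "Screening penetration will be measured by calculating the proportion of TB patients screened using PHQ-2 and their referral rates to mental health services". The Quantitative data analysis section gives the reading rule: "High screening and referral rates will indicate successful penetration of mental health assessments into the TB program". On who is screened, the article says: "TBHWs will (pre)screen all patients presenting at the selected TB centers on PHQ-2".

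**The concern.** Both outcomes belong to objective 3, and the evaluation is meant to inform scale-up in the provincial TB programme. For each, the article fixes a definition and then an indicator or rule that does not match it.

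For sustainability, the definition needs observation after the trial ends, but the logs cover only the trial. A short PHQ-2 completion time or low dropout among CBT recipients shows that the procedures were usable and that patients stayed. It does not show that the programme kept the intervention.

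For penetration, the definition concerns access among patients in need, but the rule rewards a high referral rate without saying among whom. Over all TB patients, that rate can be high because many are depressed or because the screen gives many false positives, and not only because the service reaches those who need it.

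Followed as written, the report could describe the intervention as sustained and well penetrated on figures that do not show either.

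**Working it through.** The article attaches no figure to either outcome, so there is none to reproduce. The check sets definition against indicator, then shows how an all-patient referral rate behaves.

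**Step 1: sustainability**

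| Element | Source | Period observed |
|---|---|---|
| Definition | Table 2, Sustainability row | After the trial |
| PHQ-2 completion time | Trial logs | During the trial |
| Dropout | Trial logs | During the trial |
| Follow-up adherence of CBT recipients | Trial logs | During the trial |
| Policymakers' acceptance | Said to come from the logs, but not among the listed log contents | None |

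In Table 2 the phrase about the end of the definitive trial says when the logs are retrieved. It does not set a post-trial observation period. Post-trial observations in the quantitative measure: 0. Sessions attended and intervention dropout also already serve in Table 2 as a measure of acceptability, so the same kind of log item is used for two constructs.

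**Step 2: penetration, share in need**

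If only patients in need are referred:

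all-patient referral rate = (share in need) × (referral rate among those in need)

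The Introduction gives one figure, depressive symptoms in up to 50% of TB patients. The range 20% to 50% is an assumption.

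- Need 20%, all of them referred: 0.20 × 1.00 = 20%.
- Need 50%, half of them referred: 0.50 × 0.50 = 25%.

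The second service misses half of those in need and still has the higher rate.

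**Step 3: penetration, false positives**

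If every screen-positive patient is referred:

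rate = prevalence × sensitivity + (1 − prevalence) × (1 − specificity)

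PPV = prevalence × sensitivity ÷ rate

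Prevalence, sensitivity (90%) and specificity are assumed. For prevalence 30%:

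- Specificity 90%: 0.30 × 0.90 + 0.70 × 0.10 = 0.27 + 0.07 = 34%; PPV = 0.27/0.34 = 79%.
- Specificity 60%: 0.27 + 0.70 × 0.40 = 0.27 + 0.28 = 55%; PPV = 0.27/0.55 = 49%.

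| Prevalence | Rate at specificity 90% | Rate at specificity 60% | PPV at 90% | PPV at 60% |
|---|---|---|---|---|
| 20% | 26% | 50% | 69% | 36% |
| 30% | 34% | 55% | 79% | 49% |
| 50% | 50% | 65% | 90% | 69% |

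In every row the referral rate among screen positives is 100%. The rise in the all-patient rate comes only from patients who are not depressed.

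**Step 4: screening rate**

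All presenting patients are prescreened as a trial procedure, and the 12 facilities were purposively selected. A high screening rate therefore shows largely that trial prescreening was carried out. CBT is also withheld from the control arm by design, so receipt of CBT among patients in need is limited by randomisation and not only by implementation.

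**The case against.** On sustainability, the logs are not the only evidence. The Qualitative data section says the implementation outcomes will also be explored in interviews and focus groups and triangulated with the quantitative results. The section on barriers and facilitators covers sustainability with managers, policymakers and health workers, and 8 to 12 policy-level interviews follow the last CBT session. This stands: policymakers' acceptance does have a data source, though not the logs. But these interviews explore barriers, facilitators and expectations. They do not observe continued use, so the gap between definition and measurement remains.

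On penetration, more of the objection stands. The denominator of the referral rate is never given, and an article may leave exact denominators to a fuller document. That referral is taken over all patients is an inference from the wording. The rule uses screening as well as referral and speaks only of mental health assessments, which objective 3 expressly includes; screening coverage is a partial measure of reach for these. The plan also evaluates the sensitivity and specificity of the PHQ-2, and the logs count patients screened, further assessed and given CBT, so a stepwise cascade can be built.

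A reader might therefore infer that neither indicator measures anything of its construct, or that the plan would rank an over-referring facility above a careful one. The documents do not support either. Screening coverage carries some information on reach, and no ranking of facilities on referral is planned. What remains is that the stated success rule is not tied to need, although the definition in Table 2 is.

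**Conclusion.** The sustainability point holds. The article itself fixes the definition, the source and the indicators, and the quantitative measure contains no observation of the period that the definition refers to.

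The penetration point holds in a narrower form: high referral is read as success without reference to patients in need. If the denominator is all TB patients, the rate can rise by about 20 percentage points (34% to 55% at prevalence 30%; between 15 and 24 points over prevalence 20% to 50%) through false positives alone. These sizes rest on assumed prevalence, sensitivity and specificity and on referral of every positive. They illustrate direction and scale and do not predict this trial's results.

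No estimate of the treatment effect is touched. What changes is what objective 3 can conclude about scale-up, which is enough reason to correct the text.

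**What to change.** 1. Report PHQ-2 completion time, dropout and follow-up adherence as within-trial usability and retention.
2. Keep the planned triangulation with the manager, policymaker and health-worker interviews and focus groups, but label the conclusion anticipated sustainability unless programme data from after the trial are obtained.
3. Name the interviews, not the logs, as the source for policymakers' acceptance.
4. Replace the success rule in Quantitative data analysis with a cascade from the existing logs, reported by facility: screened / presenting patients, then further assessed or referred / PHQ-2 positive. Report CBT started / randomised to CBT as within-trial uptake only, because it does not measure access among all patients in need.
5. State that screening was driven by the trial.

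The cost is mainly rewording and stated denominators. The first step of the cascade assumes that the prescreening log also counts patients who presented but were not screened. Facility TB-register counts could serve as a denominator but would be a new data source, and they are optional. The real downside is a weaker sustainability claim, which is the claim that the data can support.

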## Barriers and facilitators to sustainability and scale-up

Qualitative methods will be employed to explore the barriers and facilitators to the sustainability and scale-up of CBT therapy within routine TB control. Focus group discussions (FGDs) and semi-structured interviews (SSIs) will be conducted with key stakeholders, including TB patients who have received CBT, TBHWs involved in delivering the intervention, managers overseeing the TB control program, policymakers, and the CONTROL trial staff. Detailed methods for this objective are explained in the section below.

### Qualitative data

The implementation outcomes in this process evaluation will also be explored through SSIs and FGDs with different groups of participants. Findings from the qualitative data will be triangulated with quantitative findings to present a more authentic and holistic picture of the process.

### Data collection tool

Topic guides will be developed based on Proctor’s model of implementation outcomes [23] to guide qualitative data collection. They will then be reviewed and finalized with input from a qualitative expert, a public health expert, and members of the PPIE advisory group. These guides will serve as a structured framework to capture in-depth insight into participants’ experiences, perceptions of the intervention, the contextual and operational factors influencing its delivery, and barriers and facilitators to scale up. A total of six distinct topic guides will be developed, tailored to intervention arm patients, control arm patients, TBHWs, MOs, trial staff, and health administrators, based on their respective roles in the trial.

### Data collection and sampling

A comprehensive sampling strategy will include a wide range of insights and diverse perspectives targeting key stakeholder groups, providing an in-depth understanding of the implementation process and factors influencing the intervention's scalability. Patients who completed the intervention (attended five or all six sessions) will be sampled to conduct 10–15 SSIs at 8 weeks post-randomization, while patients who partially completed the intervention (attended 1–4 sessions) will contribute 5–10 SSIs in the same timeframe (Table 3). From a policy-level perspective, 8–12 SSIs will be conducted with TB control program managers, health administrators, pulmonology health care workers from private practice, and infectious disease program managers after the final CBT session delivery to all trial intervention arm patients. Moreover, 5–10 SSIs will be conducted with control arm patients after 24 weeks post-randomization to capture their perspectives. We will also conduct seven FGDs after 24 weeks post-randomization with TBHWs (*n* = 2), CONTROL trial staff (*n* = 3), and TB program medical officers (*n* = 2).

**Table 3 Tab3:** Qualitative data collection using topic guides based on Proctor et al.’s implementation outcomes and exploring barriers and facilitators to future scale-up

Qualitative measures			
**Group of participants**	**SSIs**	**FGDs**	**Timeline**
Patients who completed the intervention (attended five or all six sessions), the maximum variation	10–15	Nil	After 8 weeks post-randomization
Patients who couldn’t complete the intervention (attended 1–4 sessions)	5–10	Nil	After 8 weeks post-randomization
Patients in the control arm	5–10	Nil	After 24 weeks post-randomization
DOTS facilitators		02	After 24 weeks post-randomization
Medical officers		02	After 24 weeks post-randomization
Trial staff		03	After 24 weeks post-randomization
TB control program management, (ii) health administrators, (iii) TB and Pulmonology health care workers diagnosing and treating TB in private practice, and (iv) the managers of the infectious disease program	8–12	Nil	After the delivery of the final session to all the trial participants
Total	30–35	07	

All interviews will be audio-recorded using secure, encrypted digital devices to ensure accurate data capture. Recording will begin only after participants provide explicit verbal and written consent. Sessions will be conducted in private, quiet settings to maintain confidentiality and minimize disruptions. Audio recordings will be securely stored in password-protected files on encrypted devices. Access to these recordings will be restricted to authorized research team members involved in data analysis. Identifiable information will be removed during transcription to ensure participant anonymity, and all data will be securely archived following ethical guidelines.

## Data analysis

### Quantitative data analysis

We will employ descriptive and inferential statistical methods to analyse the CONTROL study and CBT intervention’s implementation outcomes—acceptability, appropriateness, adoption, and feasibility. Data from the AIM, IAM, FIM, and AMHR scales will be analysed to assess central tendencies and variability. Regression analyses will be conducted to explore relationships between implementation outcomes and participant characteristics. Retention and enrolment rates will be calculated as proportions, with chi-square tests to examine group differences.

Two independent reviewers, both experts in CBT, will assess a randomized selection of 10% of the audio-recorded CBT sessions to analyse the fidelity of the CONTROL CBT intervention through CTS-R and a CBT delivery assessment checklist. According to the Newcastle Cognitive Therapy Centre, a minimum competence standard is set at 36, with higher scores indicating greater therapeutic competence. Descriptive statistics will summarize the distribution of scores across sessions, and inter-rater reliability will be assessed using intraclass correlation coefficients to ensure consistency between reviewers. Similarly, the delivery assessment checklist evaluates adherence to the intervention’s content, and for each session, item scores will be aggregated to produce a total adherence score. Descriptive statistics will describe the adherence levels, and inter-rater reliability will be calculated to confirm reviewer consistency.

Penetration analysis will calculate the proportion of TB patients screened with the PHQ-2 and those referred for mental health services. High screening and referral rates will indicate successful penetration of mental health assessments into the TB program. Cost analysis will utilize data from the CSRI to compute the total and per-patient costs of implementing the mental health interventions. This will include direct costs (e.g., training, therapy sessions) and indirect costs (e.g., patient travel, lost productivity). The cost-effectiveness of the intervention will be evaluated by comparing the incremental costs to the health outcomes achieved, such as reductions in depression and anxiety symptoms.

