### Study design and settings

Through a concurrent mixed-method approach using quantitative and qualitative methods, we will comprehensively evaluate key implementation outcomes defined by Proctor’s framework (Table 2) [23]. The CONTROL CBT intervention will be delivered over nine months at 12 purposively selected TB care facilities (Study centers) at two study sites, districts Peshawar and Haripur, located in Khyber Pakhtunkhwa, Pakistan [15]. The selected facilities represent a mix of primary, secondary, and tertiary care settings, ensuring the intervention’s applicability and evaluation across various healthcare system levels.

Although extensively trained before the pilot phase of the trial, the TBHWs will undergo a “ten-day training course” designed to help them understand the core principles of CBT, acquire practical techniques for managing depression and anxiety in TB, and enhance their communication skills. In these trainings, master trainers, initially trained by a team comprising senior psychiatrists and a psychologist with extensive expertise in CBT delivery, will subsequently train the TBHWs to implement the intervention [15]. Medical officers (MOs) responsible for treating TB patients at each facility will receive training in the Mental Health Gap Action Programme (mhGAP). The MOs will deliver mhGAP, as enhanced treatment as usual (ETAU), to both arms of TB patients. The mhGAP training for the MOs will be delivered by a psychiatrist. This training will be based on the World Health Organization’s mhGAP intervention guide [25], ensuring alignment with standardized global mental health guidelines [15]. After each training session, participant feedback will be systematically collected to evaluate satisfaction levels. A feedback form, translated into Urdu for cultural and linguistic appropriateness, will be utilized.

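### Penetration is defined partly as spread across facilities, but the stated measures and success statement use only patient-level screening and referral rates

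*Protocol article*

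**What the plan says.** Table 2 of the protocol article describes penetration as "The extent to which the CBT intervention is institutionalized within the TB care system", and continues: "assessing its spread across healthcare facilities and the level of service access for TB patients needing psychological support". The definition thus has two parts. One has the facility as its unit (spread) and the other has the patient (access).

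The measures appear in two places. Under Penetration, sustainability and implementation costs, the subsection Data collection and sampling states: "Screening penetration will be measured by calculating the proportion of TB patients screened using PHQ-2 and their referral rates to mental health services". The Quantitative data analysis section repeats the same two quantities: "Penetration analysis will calculate the proportion of TB patients screened with the PHQ-2 and those referred for mental health services". It then adds how they are to be read: "High screening and referral rates will indicate successful penetration of mental health assessments into the TB program".

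Study design and settings gives the setting as "12 purposively selected TB care facilities (Study centers) at two study sites, districts Peshawar and Haripur", and adds: "The selected facilities represent a mix of primary, secondary, and tertiary care settings". The data collection tool subsection for penetration says that TB health workers are to pre-screen every patient who presents at the selected centres.

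**The concern.** A proportion of patients taken over all facilities weights each facility by its patient volume. It answers how many patients were reached. It does not answer at how many facilities the practice took hold. The article makes the second question part of the outcome, states no measure for it, and still gives a statement of when penetration has succeeded.

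Penetration in the routine TB programme is part of the third objective, scale-up is the subject of the fourth, and the findings are meant to inform policymakers. A conclusion of successful penetration drawn from overall rates alone could be taken to mean that screening and referral had spread across the facilities and care levels, when the figures behind it cannot show that.

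**Working it through.** **1. Definition against measure.** The article gives no expected rate, threshold or sample size for penetration, so there is no figure to reproduce. The first check sets the parts of the definition beside what is measured.

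| Part of the Table 2 definition | Unit | Stated measure |
|---|---|---|
| Level of service access | Patient | Proportion screened with PHQ-2; referral rates |
| Spread across facilities | Facility | None stated |

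The logs also count patients further assessed and patients receiving CBT, but those counts are not tied to a facility or to the success statement. That statement rests on the two patient-level rates.

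**2. Can overall rates be high while many facilities are low?** The article gives the number of facilities (12) but no volumes or rates by facility. Everything else in this step is assumed. Let k facilities perform well at rate p_hi and hold a share s of patients, and let the other 12 − k be at rate p_lo.

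- Overall rate = s × p_hi + (1 − s) × p_lo
- Unweighted facility mean = (k × p_hi + (12 − k) × p_lo) / 12

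With k = 3:

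| s | p_hi / p_lo | Overall rate | Facility mean | Median facility |
|---|---|---|---|---|
| 25% (equal volumes) | 95% / 50% | 0.25 × 0.95 + 0.75 × 0.50 = 61.3% | 61.3% | 50% |
| 70% | 95% / 50% | 0.70 × 0.95 + 0.30 × 0.50 = 81.5% | (3 × 0.95 + 9 × 0.50)/12 = 61.3% | 50% |
| 80% | 95% / 30% | 0.80 × 0.95 + 0.20 × 0.30 = 82.0% | (3 × 0.95 + 9 × 0.30)/12 = 46.3% | 30% |

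In the last two rows 9 of the 12 facilities are low, while the overall rate exceeds 80%. With equal volumes the overall rate equals the facility mean and is not inflated. Even then, one average does not say how many facilities are low.

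**3. How unequal must volumes be?** Solving for the share that gives an overall rate T: s = (T − p_lo) / (p_hi − p_lo).

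| p_hi / p_lo | T = 70% | T = 80% | T = 90% |
|---|---|---|---|
| 95% / 50% | 44% | 67% | 89% |
| 95% / 30% | 62% | 77% | 92% |
| 90% / 40% | 60% | 80% | 100% |
| 100% / 50% | 40% | 60% | 80% |

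For an overall rate of 80%, the well-performing facilities must hold about 60% to 80% of patients under these rates. A mix running from primary to tertiary care makes unequal volumes plausible, but the article does not establish them. The article does not say what counts as high, so T is assumed too.

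**4. Screening or referral?** If every presenting patient is screened as planned, every facility is at 100% and an overall screening rate hides nothing. The article states no such universal target for referral, so the mechanism in step 2 matters mainly there.

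**The case against.** The strongest reply is that the article never says the rates will be pooled and does not rule out a breakdown by centre. Tabulating a descriptive proportion by site is ordinary detail for a full protocol or SAP, neither of which is shown, and the remark that the facility mix supports evaluation at different system levels points towards such a breakdown. This is right as far as it goes. A reader might infer that the plan prescribes a single pooled proportion, but the documents do not support that: there are two rates, the success statement needs both to be high, and pooling is an inference from the absence of any facility unit. What survives is that the article does more than stay silent. It states a measure and a reading of it, and these do not cover one half of its own definition.

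Three further points have weight. Patient-level rates do measure the access half. The success sentence speaks of mental health assessments, whereas Table 2 speaks of the CBT intervention, so it may not have been meant as the rule for the whole outcome; but it is the only reading of penetration that the analysis section gives. Interviews and focus groups, to be triangulated with the quantitative results, may bring out differences between centres, though they will not give rates by facility.

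Finally, the numerical example is assumed, and widespread low screening would be a gross departure from the plan to screen everyone. That limits the point for screening. It does not remove it, since whether the intended coverage is achieved is what penetration should test.

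**Conclusion.** The point holds as a mismatch between a definition and its measure: spread across facilities is part of penetration in Table 2, and nothing stated in the measurement or analysis sections measures it. High overall rates could therefore be read as successful penetration while many of the 12 facilities are low, mainly for referral.

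The size cannot be fixed from the article. Under the assumed rates above, an overall figure just above 80% can coexist with 9 of 12 facilities at 30% to 50%, but only if volumes are strongly skewed.

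Two stronger readings are not supported. One is that success will be declared on tertiary centres alone: neither facility volumes nor the number of tertiary centres is given. The other is that scale-up would mostly reach smaller facilities: the article does not say so. The mismatch is worth correcting because it is cheap to correct and bears on what may be concluded about spread and scale-up.

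**What to change.** In Quantitative data analysis, add that screening and referral rates will be calculated for each of the 12 facilities from the existing trial logs, with the same denominators as the overall rates. Report all 12 values, with median and range, by district and care level. Base the conclusion about spread on that distribution, and keep the overall patient-level rates as the measure of service access. Reword the success sentence so that high overall rates support a conclusion about access only.

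The cost is one small additional table and no new data collection, provided that the logs identify the centre, which the article does not state. The downside is that the conclusion may be less favourable than the overall rates suggest. The change needs neither a facility-clustered interval, which would rest on 12 purposively chosen sites, nor a new rate of starting CBT.
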